### Participant recruitment

2.3

Healthy, same-sex DZ and MZ twin pairs, between the ages of 16–40yrs, were recruited to participate in the study. Recruitment started in September 2016 and was facilitated by Twins Research Australia (formerly Australian Twin Registry [33]). Twin pairs in the Metropolitan Perth-based region were sent emails, newsletters and conventional mail regarding participation in the study. Other recruitment methods included advertising in local and Perth-based newspapers, online and social media recruiting, The University of Western Australia (UWA) email lists, flyers around UWA and nearby establishments, and word of mouth. Baseline demographic data is displayed in Table 1, and a participant flow chart in Fig. 1.

**Table 1 tbl1:** Baseline characteristics of participants enrolled in the study.

		Monozygotic (MZ)	Dizygotic (DZ)
		n = 62 (31 twin pairs, 18 F, 13 M)	n = 28 (14 twin pairs, 10 F, 4 M)
		Mean (SD)	Mean (SD)
Age (yrs)	F	24.2 (5.0)	23.8 (4.2)
	M	28.0 (5.9)	22.9 (5.3)
	Total	26.2 (6.1)	23.5 (4.5)
Height (cm)	F	170.2 (4.0)	168.6 (5.9)
	M	180.8 (4.5)	178.0 (6.6)
	Total	174.5 (6.5)	171.8 (7.5)
Weight (kg)	F	67.0 (19.6)	59.3 (9.4)
	M	81.0 (12.8)	69.1 (11.3)
	Total	74.9 (18.9)	62.6 (10.9)
BMI (kg/m^2^)	F	23.0 (6.1)	20.9 (2.8)
	M	24.7 (3.6)	21.7 (2.7)
	Total	24.4 (5.3)	21.1 (2.9)

**Fig. 1 fig1:**
[figure not shown]
Participant recruitment, inclusion/exclusion, and intervention numbers. *TRA, Twins Research Australia; F, female; M, male; MZ, monozygotic; DZ, dizygotic.*

### Inclusions/exclusions, baseline testing and randomisation

2.4

The study design is illustrated in Fig. 2. Participants were required to be apparently healthy, having no signs or symptoms of congenital heart disease, ischaemic heart disease, atrial fibrillation, stroke, kidney disease, liver disease, diabetes, epilepsy, respiratory disease, exercise-induced asthma. Resting systolic (SBP) and diastolic (DBP) blood pressure had to be < 160 and < 100 mmHg, respectively, with BMI ≤ 35. Subjects were excluded if they were smokers, or had been a smoker within the last 12 months, had severe mental illness or joint, muscular or spinal injuries/disease that would prohibit intense exercise. Any serious illness that would compromise survival (e.g. cancer) was an exclusion. Subjects were also required to be untrained, defined as doing less than the minimum Australian guidelines for physical activity recommendations (<150 min week of organised exercise). They were excluded if taking any prescribed medications for previously mentioned illness/disease that would affect outcome measures of the study. Subsequent to a successful phone interview and screening, participants attended six separate testing sessions (ranging from 45 min to 2 h duration; see Fig. 3), which made up the cross-sectional portion of the study and were used as additional screening for inclusion in the subsequent longitudinal training study. Using a website (www.randomization.com), twin pairs were randomised to either END or RES training to complete their allocated exercise together as a twin pair. That is, both twins in a pair completed the same exercise modality at the same time at matched relative exercise intensities. Completing the same exercise intervention together ensured that the stimulus of the exercise was identical and time- and environment-related factors that could impact physiological adaptation (i.e. time of the year, holidays, heat of the day) did not impact on the results within a pair. This is especially important in a twin study when trying to tease apart genetic, shared and individual environmental factors as the research environment created should be as concordant as possible within each twin pair.

**Fig. 2 fig2:**
[figure not shown]
Study design schematic illustrating the longitudinal randomised cross-over exercise intervention. Monozygotic (single/solid colour) and dizygotic (multicolour) twin pairs are randomised to simultaneously participate in a 3 month supervised program, consisting of either resistance or endurance training. After a wash out period (3 months), they cross-over to complete 3 months of the alternate modality. (For interpretation of the references to colour in this figure legend, the reader is referred to the Web version of this article.)

**Fig. 3 fig3:**
[figure not shown]
Twins and exercise study structure and timetable.

### Study design

2.5

This study was approved by the UWA Human Research Ethics Committee (reference number RA/4/7031) and was prospectively registered as a clinical trial (ACTRN12616001095459) in August 2016. Baseline testing commenced in November 2016, and the exercise intervention data collection was completed in September 2019. Oral and written consent were obtained from each participant prior to participation in the study. This study conformed to the standards set by the *Declaration of Helsinki*.

The study involved baseline screening and testing of each twin within a pair. Following this, twin pairs were randomised together to participate in either the 3 month END or RES training intervention. Both twins within a pair trained at matched relative intensities for each exercise modality. Participants were tested within 2 weeks of finishing the exercise intervention. Participants then entered into a 3 month washout period where they were instructed to return to their usual level of activities as well as maintain their usual diet. Following the washout period, participants returned for pre-testing prior to crossing over and completing 3 months of their second, alternate, exercise intervention (RES or END). Again, participants post-training measures were finished within 2 weeks of exercise intervention completion (Fig. 2). Participants within a pair completed all pre- and post-assessments within 1 week of each other and completed their exercise interventions in the same time period.

Experimental measures included body composition assessment, cardiorespiratory fitness, muscular strength, physical activity, food diaries and appetite-related questionnaires, biochemistry analysis, peripheral vascular assessments, pulse wave analysis and velocity assessments, cerebrovascular assessments, cognitive testing, sleep, anxiety and general health questionnaires, cardiac magnetic resonance imaging (MRI), echocardiograms, girth measurements and resting blood pressures (Fig. 3).

Throughout the duration of the study, participants were instructed to maintain their current lifestyle as much as possible, that is, to continue their current diet and exercise routine in addition to the three exercise sessions per week performed at UWA as part of the study. Compliance was assessed using activity monitors and food diaries. This maintenance was to ensure that changes throughout the study were due to the exercise intervention, rather than external influences.

### Exercise training protocols

2.6

Exercise interventions were centre-based and supervised by a qualified sport scientist or an accredited exercise physiologist (AEP). Sessions were either in the morning or late afternoon/evening to avoid the heat of the day and to accommodate participant work schedules. Participants attended three exercise sessions a week at UWA. A standardised warm up and cool down were conducted in each session. If an injury prevented an individual from completing their prescribed exercise, then that individual and their twin were to complete a modified exercise instead. This ensured that twin pairs were receiving equivalent physiological stimulation throughout the study. Adherence to the training program was required to be 80% or higher across both interventions in order for the twin pair to be included in final analyses.

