
## Planned statistical analysis

3

Statistical analyses are to be performed with SPSS 20.0 (IBM Australia Ltd, New South Wales, Australia) and STATA 11 software (StataCorp, College Station, Texas). All data will be reported as group means with confidence intervals, with default statistical significance assumed at *P* < 0.05. Cross-sectional results for each outcome measure refer to baseline entry (week 0) data. Response to training data is post minus pre for END and RES training. Normality of groups (MZ and DZ) will be assessed via Shapiro-Wilk test of normality where normality of spread is assumed at *P* > 0.05. Between-group (MZ vs DZ) differences will be assessed with the conservative non-parametric Mann-Whitney *U* test and regression models including the single covariate zygosity (MZ/DZ), fitted using a generalised estimating equation (GEE) approach to account for correlation of twins within-pairs. The effect of the exercise interventions on each outcome measure will be assessed using a linear mixed models approach.

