### Sample size and power

3.2

Power analysis is based on our primary outcome measures which are highly specialized and sensitive; vascular function (FMD), cardiac and cerebrovascular adaptation. Our cardiac publications [6,8,9] have reported significant effects in fewer subjects (n = 10 and n = 13 per group) than we recruited in the present study; we observed highly significant differences utilising highly sensitive MRI. Regarding cerebral measures, previous publications and our pilot work demonstrate that cerebral blood flow is increased in older individuals (n = 9, 65–78 yrs) by 10% after intervention. Our previous twin study publications in a paediatric population [24,31] cross-sectionally revealed FMD correlations of 0.6 and 0.38 in MZ and DZ twin pairs, respectively, in a smaller sample size of 22 (11 pairs) per group [24]. In addition, this study applied an exercise intervention (8 weeks) shorter than the current study (12 weeks), and produced correlations of 0.74 and 0.37 for FMD responses in MZ and DZ groups (n = 24–6 pairs per group) [31]. A power analysis (G*Power v3.1.2), performed using the predicted correlations for rMZ = 0.80 and rDZ = 0.30, assuming alpha = 0.05, indicates that a sample size of 23 individuals in each group provides 80% power.

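### The 80% adherence rule for final analyses, read literally, removes week-0 data that adherence cannot affect and lets attendance in one mode remove response data from the other

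*Protocol article*

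**What the plan says.** Section 2.6 (Exercise training protocols) closes with the inclusion rule: adherence was "required to be 80% or higher across both interventions in order for the twin pair to be included in final analyses". The unit excluded is the pair and the period covered is both interventions. Adherence is observed after allocation, since section 2.5 says that "twin pairs were randomised together to participate in either the 3 month END or RES training intervention" and training followed.

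Section 3 defines three separate kinds of data. For the first, "Cross-sectional results for each outcome measure refer to baseline entry (week 0) data". The other two are the END response and the RES response, each post minus pre. The primary objective is to estimate rMZ, rDZ and the A, C and E components for each of the three. Sections 3 and 3.1 do not mention the adherence rule.

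Table 1, titled "Baseline characteristics of participants enrolled in the study", gives MZ as "n = 62 (31 twin pairs, 18 F, 13 M") and DZ as "n = 28 (14 twin pairs, 10 F, 4 M"). The power statement in section 3.2 was "performed using the predicted correlations for rMZ = 0.80 and rDZ = 0.30, assuming alpha = 0.05". It mentions no allowance for pairs excluded on adherence.

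**The concern.** The rule ties together data that the analysis keeps apart.

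- **Week-0 data.** These were collected before any training. Later attendance cannot make them less valid, yet the phrase about final analyses does not exempt them.
- **The other modality.** END and RES responses are separate quantities with separate variance components. Poor attendance in RES does not spoil a well-attended END period. Only END–RES concordance needs both modes.
- **The co-twin.** Because the pair is the unit, one twin's attendance can remove both.

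Two things are at stake. The first is precision, which is weakest among the 14 DZ pairs. Section 3 calculates A only when rMZ and rDZ differ significantly, so lost power pushes outcomes towards the model with C and E only. The second is selection. Attendance may plausibly be related to fitness, tolerance of training or family, so response rates and twin correlations in the retained pairs may not describe all the pairs that trained.

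**Working it through.** **Inputs from the article.** 31 MZ and 14 DZ pairs (Table 1); rMZ = 0.80, rDZ = 0.30, alpha 0.05 with sidedness not stated, and 23 per group for 80% power (section 3.2); 0.74 and 0.37 as earlier FMD-response correlations (section 3.2). **Assumed:** the chance p that a twin reaches 80% in a given mode, because the text reports no adherence.

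**Step 1. The plan's own figure.** Fisher z: q = atanh(0.80) − atanh(0.30) = 1.0986 − 0.3095 = 0.789.
- One-sided: n = 2 × ((1.645 + 0.842)/0.789)² + 3 = 22.9, so 23. This reproduces the stated figure.
- Two-sided: n = 2 × ((1.960 + 0.842)/0.789)² + 3 = 28.2, so 29. This does not.

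Each pair contributes one point to a correlation, so the pair is the unit used below.

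**Step 2. All enrolled pairs kept.** Power = Φ(q/√(1/(n₁−3) + 1/(n₂−3)) − 1.96).
With 31/14: √(1/28 + 1/11) = 0.356; 0.789/0.356 = 2.22; power 60% two-sided (72% one-sided).

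**Step 3. What the rule could cost.** Read per twin and per mode, the share of pairs kept is p if twins and modes always agree, p² if twins agree but modes are independent, and p⁴ if all four are independent. Cells show MZ/DZ pairs kept and two-sided power for 0.80 against 0.30.

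| p | Twins and modes agree (p) | Twins agree (p²) | All independent (p⁴) |
|---|---|---|---|
| 0.95 | 29/13, 56% | 28/13, 56% | 25/11, 48% |
| 0.90 | 28/13, 56% | 25/11, 48% | 20/9, 38% |
| 0.80 | 25/11, 48% | 20/9, 38% | 13/6, 22% |

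Example, 20/9: √(1/17 + 1/6) = 0.475; 0.789/0.475 = 1.66; Φ(1.66 − 1.96) = 38%.

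For 0.74 against 0.37 (q = 0.562), all enrolled pairs give 35%. At p = 0.90 the three columns give 32%, 28% and 22%.

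**Step 4. How the 80% is counted.** The article does not say whether the 80% is pooled over modes or applies to each, or whether it is taken per twin or per pair. With equal session numbers, illustrative attendances of 75% and 90% pool to 82.5%: the pair stays under a pooled rule and goes under a per-mode rule. Attendances of 60% and 90% pool to 75%: the pair goes under both, and the well-attended mode goes with it. So data from the adherent mode can be lost under either reading.

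**The case against.** Four points on the other side have weight.

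1. **The week-0 loss may not be intended.** The rule sits in the section on training. Section 2.4 describes baseline testing as the cross-sectional part of the study, distinct from the later training study, and section 3 attaches no adherence condition to week-0 data. This is probably what was meant, but the wording of section 2.6 does not say so.

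2. **No loss is documented.** A reader might infer that the rule has already reduced the 14 DZ pairs. The text does not support that: it gives no adherence figures or exclusion counts, and the flow chart (Fig. 1) is not available here.

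3. **The harshest power figure fits the design poorly.** A reader might take the fall from 60% to 38% as the effect of the rule. At p = 0.90 it requires four independent chances, whereas twins trained together under supervision, and an injured twin's co-twin also did the modified exercise. The 48% to 56% range is more plausible there. The starting 60% comes from having 14 DZ pairs and is a separate matter.

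4. **A per-protocol set suits the aim.** The design rests on both twins receiving an identical stimulus. Unequal attendance within a pair adds unshared variance and lowers both correlations; familial attendance could pass for heritable response. The MZ–DZ contrast is not randomised, since randomisation fixed only the order of modes. A reader might infer that an all-randomised set must be primary; the documents do not support that. Further analysis sets may also lie in an analysis plan that is not shown, so their absence from the article is not the complaint.

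Points 2 to 4 limit the size of the concern and the strength of the remedy. They do not explain why week-0 data, or END data from a pair with poor RES attendance, should depend on this rule.

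**Conclusion.** The point holds as a fault in how a fixed rule is worded and scoped. Followed literally, it can discard week-0 data that attendance cannot affect, and response data from a mode that was well attended. The second loss is possible whether the 80% is pooled or counted per mode.

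The size is conditional. Against about 60% two-sided power with all enrolled pairs, an assumed 0.90 chance per twin and mode gives about 56%, 48% or 38%, depending on how far adherence agrees between twins and modes. These figures rest on the Fisher-z approximation (the plan itself uses a likelihood-ratio test), on a two-sided 5% level, on a per-twin, per-mode reading of the rule and on assumed adherence. Any selection bias is plausible but cannot be sized from the text. The 80% set is a defensible choice for the response analyses; its reach into the other data is not.

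**What to change.** 1. **Cross-sectional analyses:** use all DNA-typed pairs with week-0 data, and state that the adherence rule does not apply to them.
2. **Response analyses:** apply the 80% criterion separately to each modality, so that END data are never removed because of RES adherence or the reverse. Require both modes only for END–RES concordance. State whether the 80% is counted per twin or per pair.
3. **Beside the 80% set:** report an analysis of all randomised pairs with pre and post data in that modality, whatever their attendance.

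Which response set is primary may remain the sponsor's choice.

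The cost is a reworded rule and some extra analysis, with no new data. In the all-pairs set the mean effect may be diluted, and unshared or familial attendance-related variance may enter the twin correlations. Reporting the two sets side by side shows how much the results depend on the rule.

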#### Endurance (END) training

2.6.1

The two exercise modalities (END and RES training) were chosen as they provide distinct haemodynamic and physiological stimuli for adaptation. The exercise interventions were intensity matched and progressively overloaded throughout the 12 week programs.

Training intensity was personalised and matched within the twin pair for each session and monitored via continuous heart rate (HR) assessment. Target HRs were calculated from HR at a percentage of the initial graded exercise VO_2_max test, so that they were individualised, but matched, for intensity between individuals and within-twin pairs. During each exercise session, intensity was monitored continuously using a HR monitor (Polar RS300X HR monitor, Polar Electro Oy, Finland) and recorded at regular intervals. This allowed the trainer to ensure participants were working at their specified HRs for each session. Participants completed two running sessions and one cycling session per week. Running sessions took place on the UWA 200 m grass track, and cycling sessions took place in the UWA laboratory/gym on cycle ergometers (Ergomedic 828 E, MONARK, Vansbro, Sweden). Duration and intensity progressively increased over the course of the 3 month exercise intervention from 15 min, to 60 min of exercise.

The 12 week END program followed a periodised progressive macrocycle plan consisting of three mesocycles of 4 weeks each. The first mesocycle, the ‘general preparatory’ phase (weeks 1–4), consisted of low training intensity/volume (lots of walking/jogging at 60% HR, 1–2.5 km running and/or 15–25 min cycling/running) including a long warm up focusing on running drills, technique and dynamic stretching. The second mesocycle, the ‘high intensity’ phase (weeks 5–8), consisted of higher intensity work with higher HRs (up to 90%), and distance/duration (2.5–5 km running and/or 25–40 min cycling/running). The final mesocycle, the ‘maintenance and distance’ phase (weeks 9–12), consisted mostly of maintaining sub-threshold HRs (70–85%) for longer distance/duration (5–7 km running and/or 40 min in week 9–60 min by week 12 cycling/running). In the mesocycles, a 1:1 structure loading existed with a ‘hard’ loading week followed by an ‘easier’ or ‘maintenance’ week. Within each week there existed a structured load with a ‘harder’ run session, an ‘easier’ run session and the cycling session was always the longest duration session in each week, adapting many principles from previously published work [8,34].

#### Resistance (RES) training

2.6.2

Number of repetitions, number of sets, weight and rate of perceived exertion (RPE) were recorded for every session to allow the trainers to monitor the work load undertaken by the participants. The main purpose of this monitoring was to ensure individual workload was equal within twin pairs. Specific exercises, number of sets and number of repetitions was standardised across all participants. However, individual weights were prescribed from each participants pre-training one repetition maximum (1RM). The 12 week RES training program also followed a periodised plan consisting of four mesocycles of 3 weeks each, as shown in Table 2. The first mesocycle focused on muscular endurance (weeks 1–3) where intensity was low (60–70% 1RM), reps were high (12–15 reps) and rest periods between sets was short (30–60s). This first few weeks allowed participants to focus on forming good technique habits, condition muscles and assist recovery between sessions. The second mesocycle was muscular hypertrophy (weeks 4–6) where intensity increased (70–75%), reps decreased (10–12 reps), but rest periods remained short between sets (30–90s). Weeks 7–9 was a progressive step between muscular hypertrophy and strength where intensity increased (75–80%), reps decreased (8–10 reps) and rest periods between sets increased (1–2 min). The last mesocycle focused on improving muscular strength where intensity increased (80–90%), reps decreased (5 reps) and rest periods between sets increased (3–5 min).

**Table 2 tbl2:** Resistance training breakdown of mesocycles.

Weeks	Training Type	Intensity (%1RM)	Repetitions	Rest
1–3	Muscular Endurance	60–70%	12–15	30–60s
4–6	Hypertrophy	70–75%	10–12	30–90s
7–9	Hypertrophy/Strength	75–80%	8–10	1–2 min
10–12	Strength	80–90%	5	3–5 min

Each session focussed on one of the five main exercises (two upper body – bench press and standing military press; three lower body – squats, deadlift and leg press) that were rotated alternating upper and lower body on separate days. There were secondary exercises performed during each session that used muscle groups that were similar to, or would assist in performing, the main exercise of the session (i.e. staggered feet leg press, seated row, lat pulldown). Participants performed a standardised warm up before completing their session and a standardised 5 min core exercises and cool down at the end of the session. To guide participants progressions, 1RM assessments were repeated half way through their 12 week program.

### Outcome measures

2.7

#### Zygosity DNA testing

2.7.1

A DNA cheek swab was obtained following written consent during the participants’ first testing session to determine zygosity of twin pairs for inclusion in the study (EasyDNA AU, Springwood, QLD). Four swabs were taken in total, two swabs on each side of the participants mouth, rubbed ten times against the inside of the participants cheek. Participants collected, packaged and sealed their own samples to eliminate the risk of cross-contamination. Samples were sent to an independent genetics laboratory for testing of zygosity as the probability based on genetic markers of twin pairs being either MZ or DZ. Participants elected whether they would receive the results of the DNA test. When initially recruiting for the study twin pairs self-reported their zygosity, however when they were DNA zygosity tested 10 self-reported DZ twin pairs were actually found to be MZ. Therefore, DNA zygosity testing was a major strength within the current study as heritability is determined based on zygosity. Nearly 25% of twin pairs self-reported zygosity was incorrect in our study and our results could have been very different if DNA samples had not been acquired. A systematic review and meta-regression has also concluded that self-reported rather than DNA tested zygosity has a significant effect on heritability results [35].

